The primary outcome, prostate cancer-specific mortality at a median of 15 years' follow-up, was reached on 23rd November 2021, in parallel with completion of 12-years follow-up for patient-reported outcome measures (PROMs). These findings are still confidential, pending submission to a leading journal. However, a meeting with the Trial Steering Committee in January 2022 confirmed these median 15-year results underpin the need for further follow-up for a median of 20 years. This additional follow up of clinical primary and secondary outcomes only (not PROMs) will further extend understanding of the impacts of treatment and provide essential information for policy and treatment decision-making for men newly diagnosed with localised prostate cancer.

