### 24.1 Primary Outcome

The primary outcome is definite or probable prostate cancer specific mortality (including definite or probable intervention-related mortality) at a median of 10, 15, and 20 years following randomisation.

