#### *Extended follow-up from 2018 to March 2027*

The statistical methods and analysis for the primary analyses were described in the published version of the protocol and Statistical Analysis Plan, published on <http://hdl.handle.net/1983/14265b05-5d00-40b2-90c7-020db8ee725a>. Analyses for the median 15 year analyses are detailed below and were reviewed by the NIHR HTA in the extension funding application The 15 year median analysis Statistical Analysis Plan is published at <https://doi.org/10.17605/OSF.IO/JCT49>. Analyses for the 20 year median analyses will follow similar approaches as for the 15 year analyses.

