### **Description of Statistical Methods (2018 to March 2027)**

The statistical analysis of primary and secondary outcomes conducted for the median 10-year follow-up will be repeated for the median 15-year and 20 year follow-up. In brief, the primary outcome of deaths due to prostate cancer or its treatment will be compared among the three assigned treatment groups on an intention-to-treat basis with the use of Cox proportional hazards regression adjusted for trial centre, age at baseline, Gleason score, and PSA level at baseline (log-transformed). The results of a cumulative incidence

approach, which will avoid bias due to other causes of death, will also be presented (although there was no evidence of such bias in the primary 10-year analysis). This approach will be adapted as necessary for secondary event-based outcomes, e.g. date of disease progression, date of diagnosis of metastatic disease, and all-cause mortality. The previously specified sub-group analyses will be conducted, investigating whether the relative treatment effects vary by age, clinical stage, Gleason score, and PSA level at diagnosis. Patient reported outcomes completed during the complete 11-year follow-up will be compared among the three assigned treatment groups on an intention-to-treat basis. Two-level random-effects models will be used to accommodate the correlation between the repeated assessments for each man. Two-level linear models will be used for continuous measures, and two-level logistic models were used for binary measures. All models will include trial centre, age at baseline, Gleason score, and PSA level at baseline (log-transformed) as covariates. All men with at least one post-randomisation measure available will be included in an analysis; there are no plans to impute missing assessments, although the possible effect of these on the observed results will be investigated through sensitivity analyses.

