## 6.2. Primary analysis

The primary analysis will be conducted on an intention-to-treat basis comparing treatment groups as allocated. Deaths occurring until a median of 10-year follow-up has accumulated (midnight 00:00 on Monday 23rd November 2015) will be included in the locked database.

The primary outcome measure of prostate cancer (definite, probable, or intervention-related) mortality will be compared between the three treatment groups using Cox's proportional hazards regression adjusted for study centre (all nine centres distinguished using dummy variables), age at baseline (continuous measure in years), Gleason score (2-6, 7, 8-10), and PSA at baseline (continuous measure in ng/ml, log-transformed to accommodate positive skewed distribution):

$$h(t) = h_0(t) \exp\{\beta_{1j}x_{1i} + \beta_{2k}x_{2i} + \beta_3x_{3i} + \beta_{4m}x_{4i} + \beta_5 \ln(x_{5i})\}$$

$\beta_{1j}$  is the log hazard ratio comparing two of the treatment arms, with two of the three pairwise comparisons being available from a single iteration of the analysis (i.e.  $j=1,2$  the estimated comparisons depending on the choice of comparator treatment).  $x_{1i}$  is the treatment allocation (0,1,2) for participant  $i$ .  $\beta_{2k}$  ( $k=1$  to 8) captures differences in the hazard of the primary outcome event between study centres,  $x_{2i}$  being the study centre for participant  $i$ .  $\beta_3$  is the linear effect of age, with  $x_{3i}$  being the age in years for participant  $i$ .  $\beta_{4m}$  ( $m=1,2$ ) accommodates the effect of Gleason score category with  $x_{4i}$  being the Gleason score category for participant  $i$ . Finally  $\beta_5$  is the linear effect of log-transformed PSA level,  $x_{5i}$  being the PSA level at diagnosis for participant  $i$ .

The hazard ratio and 95% confidence interval for the treatment effect estimated in each pairwise comparison of allocated treatments will be presented, but pairwise significance tests will only be conducted if a test of an equal 10-year disease specific mortality risk across all three arms yields a p-value of less than 0.05 (Table 3). This conditional approach keeps the overall false positive rate at 5%, and has been found to maintain power in simulation studies (Bauer 1991).

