## 2.9. Outcome measures

### 2.9.1. Primary outcome

The primary outcome is definite or probable prostate cancer mortality, including intervention-related deaths, at a median 10 years' follow-up.

*We will repeat the analysis of definite or probable prostate cancer mortality, including intervention-related deaths, at 10 years (with all participating men having more than 10 years' follow-up) and at the median 15 years' follow-up.*

*As previously the plan is for the primary outcome measure to be determined by the independent cause of death committee. If this proves not possible, we will rely on certified underlying cause of death where necessary.*

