The hazard ratio and 95% confidence interval for the treatment effect estimated in each pairwise comparison of allocated treatments will be presented, but pairwise significance tests will only be conducted if a test of an equal 15-year disease specific mortality risk across all three arms yields a p-value of less than 0.05 (Table 3). This conditional approach keeps the overall false positive rate at 5% and has been found to maintain power in simulation studies (Bauer 1991).

The competing risk of all-cause death is not anticipated to influence the estimation of the treatment effect on the risk of prostate cancer mortality. Age is the only strongly influential risk factor shared by all-cause and prostate cancer mortality, and age is included as a covariate in all models.

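### Three analyses are called primary, each tested at 5%, and the documents disagree on which is primary; the stated 5% false positive rate holds within one analysis but is about 10–12% across the three

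*Supplement*

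**What the plan says.** **Which duration is primary.** The current texts differ.

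| Place | Primary at median |
|---|---|
| Protocol v5.5, synopsis | 20 years |
| Protocol, 22.8 Survival Data | 10 and 15 years (no median stated) |
| Protocol, 6 Objectives and 24.1 Primary Outcome | 10, 15 and 20 years ("at a median of 10, 15, and 20 years following randomisation") |
| Protocol, 29 Publication Policy | 10, 15 and 20 years, all called primary analyses |
| 15-year SAP, 2.1.1 and 2.9.1 | 10 years |

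The SAP wording is: "The primary outcome is definite or probable prostate cancer mortality, including intervention-related deaths, at a median 10 years' follow-up". It then describes the later analysis as a repeat.

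**How each analysis is tested.** The 10-year SAP (6.2) and the 15-year SAP (5.2) use the same rule. A three-arm test comes first, and pairwise tests follow only if it gives p<0.05. For 20 years, protocol Appendix 2 says: "Analyses for the 20 year median analyses will follow similar approaches as for the 15 year analyses". It adds that the analysis "conducted for the median 10-year follow-up will be repeated for the median 15-year and 20 year follow-up".

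**The error claim.** "This conditional approach keeps the overall false positive rate at 5" per cent. The sentence appears in both SAPs and in protocol Appendix 2 (Presentation of the primary analyses), so it shares a document with the three-duration primary outcome.

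**The extension.** Protocol 3.1 (Updated background, 2022) reports that a steering committee meeting in January 2022 "confirmed these median 15-year results underpin the need for further follow-up for a median of 20 years".

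**The concern.** Under protocol v5.5 there are three opportunities to declare a primary result, all on the same accumulating deaths and each apparently at 5%. A reader who takes the 5% sentence as the error rate for the primary objective would be misled, because no section adjusts for the repeated analyses.

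The disagreement over which duration is primary has a practical consequence. If p first falls below 0.05 at 20 years, protocol 24.1 makes that a primary-outcome finding. Under the 15-year SAP's definition it would be a descriptive update of a primary question already answered at 10 years. The 20-year analysis is still to come, so the label can be fixed before the data are seen.

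**Working it through.** **Inputs**
- Randomised: 545, 553 and 545 (protocol Appendix 2, The Number of Participants).
- Deaths at median 10 years: 8 + 5 + 4 = 17 (same place).
- Deaths projected by the end of 2020, the 15-year census: 34 (same place, simple extrapolation).
- Deaths at 20 years: not given. The range 48–72 is assumed. It borrows counts that Appendix 2 uses for conditional power, not for 20 years.
- Level: p<0.05 at 10 and 15 years as stated; 0.05 at 20 years inferred from the two Appendix 2 sentences.

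**Step 1: reproduce the stated 5%.** For one analysis with three equal arms, I simulated the three-arm chi-square test on 2 df (critical value 5.99) followed by pairwise tests at two-sided 5%. With no difference anywhere, the false positive rate is 5.0%. With one arm truly different, the remaining null pair is falsely rejected at most 5.0% of the time. Three pairwise tests without the preliminary test would give 12.2%. The sentence is right for one analysis.

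**Step 2: three analyses.** The three-arm statistic was simulated as a two-dimensional score process S with independent increments and variance proportional to deaths d. Analysis k rejects if |S_k|²/d_k > 5.99. The table gives the cumulative probability of at least one rejection when the arms do not differ.

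| Deaths at 10 / 15 / 20 years | After 10 | After 15 | After 20 |
|---|---|---|---|
| 17 / 34 / 48 | 5.0% | 8.4% | 10.7% |
| 17 / 34 / 60 | 5.0% | 8.4% | 11.3% |
| 17 / 34 / 72 | 5.0% | 8.4% | 11.6% |
| 17 / 48 / 96 | 5.0% | 8.9% | 12.0% |
| Information proportional to years (10 / 15 / 20) | 5.0% | 7.8% | 9.9% |

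Outer bounds: 1 − 0.95³ = 14.3% if the three tests were independent, and 3 × 5% = 15% by Bonferroni. A constant level of about 0.020–0.022 at all three analyses would have held 5% overall.

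**Step 3: what remains after the 10-year result.** Expected deaths under no difference are 17 × 545/1643 = 5.64, 17 × 553/1643 = 5.72 and 5.64. The crude chi-square is (8−5.64)²/5.64 + (5−5.72)²/5.72 + (4−5.64)²/5.64 = 0.99 + 0.09 + 0.48 = 1.56 (p = 0.46). Simulating forward from that point with no difference, the chance of p<0.05 at 15 or 20 years is about 5–7%. The chance that it first appears at 20 years is about 2–3%.

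**Step 4: a stricter later threshold.** With the 10-year test at 0.05 and both later tests at 0.01 (deaths 17/34/51), the total is 6.0%. With both at 0.001 it is about 5.1%. The 10-year test has already used the full 5%, so any later confirmatory test takes the total above it.

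**The case against.** **The sentence is not false.** It refers to the rule just before it, for pairwise tests within one analysis, and Step 1 confirms it there. No section expressly claims 5% across durations. This stands. What fails is only the wider reading, which the word overall invites once the same protocol names three primary analyses.

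**The SAP already keeps 10 years as primary.** It calls the later analysis a repeat and presents hazard ratios with 95% intervals whatever the test shows. This also stands, and it is why the fix follows the SAPs. It does not remove the conflict, because protocol v5.5 is the later document and says otherwise in several places.

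**The remaining risk is smaller than 11%.** Given the 8/5/4 split at 10 years, the chance of a later false positive is about 5–7%. That is correct, and the 10–12% describes the three-analysis procedure as a whole. It still leaves the later primary claims without any stated error rate.

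**Longer follow-up was foreseen.** The 2001 protocol had 15-year survival as an objective and five-yearly survival among its secondary outcomes. The 15-year SAP (2.10) states that no data accrued since the 10-year publication had been analysed when it was written. A reader might infer that extending on sight of the 15-year results inflates the error further. It does not: the three-analysis rate already counts a rejection at any of the three. The extension is only a reason not to present the 20-year analysis as an unqualified primary test.

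**Conclusion.** The point holds as a matter of labelling and of the scope of one sentence. Protocol v5.5 names three primary analyses, its own sections and the SAP disagree on which duration is primary, and no rule covers repeated testing. Across the three analyses the false positive rate is about 11% on the counts used (10.7–11.6%), and about 10–12% over wider assumptions, against 5% within each.

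This rests on an assumed 20-year death count and an inferred 5% level at 20 years; a 20-year SAP could still set something different. The median 10-year analysis taken alone holds its 5%. The documents do not support reading the 5% sentence as a miscalculation.

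**What to change.** 1. In the protocol, reconcile the synopsis, section 6, 22.8, 24.1 and section 29 with the SAPs, so that the median 10-year analysis is the single confirmatory primary analysis.
2. Label the 15- and 20-year analyses as extended follow-up. Report hazard ratios, absolute risks and 95% confidence intervals, and state that p-values are not controlled across durations.
3. In protocol Appendix 2, and in the 20-year SAP when written, reword the error sentence to say that the false positive rate is kept at 5% within this analysis.
4. A reduced 20-year threshold should not be offered as making that analysis confirmatory at 5% overall (Step 4). If a formal 20-year test is wanted, state its level and the resulting total error rate before the 20-year data are seen.

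The cost is wording only, with no change to follow-up, data or treatment. The downside is that the later results carry a weaker label.

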### **The Number of Participants**

The original sample size calculation was presented in published protocol. The ProtecT study randomly allocated 545 men to active monitoring, 553 men to surgery, and 545 men to radiotherapy. Amongst these men, at median 10-year follow-up, there were 8, 5 and 4 prostate cancer deaths respectively. There were very few withdrawals at the time of the median 10-year analyses in randomised men. A simple extrapolation from the occurrence of prostate cancer deaths during the median 10-year follow-up, suggests that by the end of 2020 the number will have doubled from 17 to 34 among those randomised. If there is an increase in the incidence rate of prostate cancer death, as may result from the number of metastatic disease cases that have been diagnosed, then conditional power of 67%, 78%, and 85%, would result from the occurrence of 48, 60, and 72 prostate cancer deaths respectively.

A formal sample size calculation was not undertaken for men in other groups (advanced cancer, comorbidities or with and initial PSA of 20ng/ml or above). All men in these groups will be followed up observationally.

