## 5. ANALYSIS OF EFFECTIVENESS

### 5.1. Summary of outcomes to report at median 15 years follow-up

The following summaries of the outcome events will be presented for each treatment allocation group:

- Number of deaths due to prostate cancer.
- Prostate cancer mortality at 15 years, with 95% confidence interval.
- Prostate cancer mortality per 1,000 person years of follow-up, with 95% confidence interval.
- Kaplan-Meier survival of death from prostate cancer as a function over time.

The following summaries will be presented for the clinical secondary outcome events:

- Number of events.
- Events per 1000 person years of follow-up, with 95% confidence interval.
- Kaplan-Meier overall survival and survival free of disease progression as functions over time

In addition, if the data can be obtained, the Kaplan-Meier cumulative incidence of the uptake of radical treatment will be presented for the three treatment groups as a function over time.

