## 7. FINAL REPORT TABLES AND FIGURES

**Figure 1.** CONSORT flowchart, illustrating the flow of participants through each of the three arms of the trial, from the point of randomisation.

[figure not shown]

**Figure 2.** Kaplan-Meier estimates of the cumulative probability of undergoing radical interventions during the follow-up period, according to treatment group.

Radical intervention was defined as a radical prostatectomy, per-protocol radiotherapy, non-protocol radiotherapy (including brachytherapy), or high-intensity focussed ultrasound therapy.

**Figure 3.** Kaplan-Meier estimates of prostate cancer-specific survival and freedom from disease progression, according to treatment group: active monitoring (solid line), surgery (long dash line) and radiotherapy (short dash line) treatment groups

Panel A shows the rate of prostate cancer-specific survival. Prostate cancer-specific deaths were those that were definitely or probably due to prostate cancer as determined by an independent cause-of-death evaluation committee whose members were unaware of treatment assignments.

Panel B shows the rate of overall survival.

Panel C shows the rate of freedom from disease progression. Clinical progression of prostate cancer included metastases and death due to prostate cancer or its treatment.

**Table 1.** Prostate cancer mortality, Clinical progression, metastatic disease and all-cause mortality, by randomised group

|                                                                     | Active monitoring protocol
(N=545) | Surgery
(N=553) | Radiotherapy protocol
(N=545) | p-value  |
|---------------------------------------------------------------------|---------------------------------------|--------------------|----------------------------------|----------------------|
| Total person years in follow-up                                     |                                       |                    |                                  |                      |
| Number of deaths due to prostate cancer                 |                                       |                    |                                  |                      |
| % prostate cancer mortality at median 10 years (95% CI)             |                                       |                    |                                  |                      |

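### The 15-year SAP plans Kaplan-Meier curves for prostate-cancer death, progression and radical-treatment uptake and omits the cumulative incidence analysis promised in Protocol 5.5, so these absolute risks would come out somewhat too high

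*Supplement*

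**What the plan says.** **15-year SAP, section 5.1.** The outcome summaries include "Kaplan-Meier survival of death from prostate cancer as a function over time". Overall survival and progression-free survival are also to be shown by Kaplan-Meier. Subject to data availability, the plan adds: "the Kaplan-Meier cumulative incidence of the uptake of radical treatment will be presented for the three treatment groups as a function over time". A 15-year prostate-cancer mortality percentage with a confidence interval is listed as well, but no estimator is named for it, either there or in the percentage rows of Table 1.

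**15-year SAP, section 7.** Figure 2 shows radical intervention by Kaplan-Meier. Figure 3 gives "Kaplan-Meier estimates of prostate cancer-specific survival and freedom from disease progression, according to treatment group". The legend to panel C counts metastases and deaths from prostate cancer or its treatment as progression. It does not list deaths from other causes.

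**15-year SAP, section 5.2.** After the Cox model and the rule for pairwise tests comes the only competing-risk statement: "The competing risk of all-cause death is not anticipated to influence the estimation of the treatment effect on the risk of prostate cancer mortality". The reason given is that age is the one strong risk factor shared by both kinds of death and is a covariate in all models.

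**Protocol 5.5, Appendix 2, Description of Statistical Methods.** For the 15- and 20-year analyses, a cumulative incidence "approach, which will avoid bias due to other causes of death, will also be presented". The protocol adds that no such bias was evident at 10 years, and that the approach will be adapted as necessary to secondary events, including progression and metastatic disease.

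**The concern.** A man who dies of heart disease can no longer die of prostate cancer, progress or have radical treatment. A Kaplan-Meier curve that censors him treats him as still at risk. One minus that curve then estimates a risk in a world without other deaths, and this exceeds the proportion of men who actually have the event.

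Men entered at 50-69 years and are followed for 15 years or more. The protocol's updated background (section 3.2) itself describes the risk of death from other causes as higher than that from prostate cancer. The same section says the results are meant to inform the trade-off between disease outcomes and side effects, and readers make that trade-off on absolute risks.

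The age-covariate argument cannot help here: it concerns a regression coefficient, and the planned curves are by treatment group with no adjustment stated. The statement in 5.2 also names the competing event as all-cause death, which includes the outcome itself. Finally, an analyst following the SAP alone would not produce the analysis the protocol promises.

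**Working it through.** **Inputs from the documents (Protocol 5.5, Appendix 2)**
- Men randomised: "The ProtecT study randomly allocated 545 men to active monitoring, 553 men to surgery, and 545 men to radiotherapy", so 545 + 553 + 545 = 1643.
- At median 10 years: "there were 8, 5 and 4 prostate cancer deaths respectively", so 17 in all.
- By the 15-year census, a simple extrapolation "suggests that by the end of 2020 the number will have doubled from 17 to 34 among those randomised". The conditional-power scenarios use 48, 60 and 72 deaths.
- Design assumption of about 85% overall survival at 10 years.

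**Assumptions not in the documents.** Other-cause death of 15-25% by 15 years. As a guide, a constant hazard with 85% survival at 10 years gives 1 - 0.85^1.5 = 21.6% dead by 15 years. The progression and uptake levels and the hazard shapes below are also assumed. Deaths/1643 is treated as the 15-year cumulative incidence.

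**Step 1: reproduce the documents' figure.** 17/1643 = 1.03%, matching the roughly 1% quoted for 10 years. If other-cause death by then were 10-15%, one minus Kaplan-Meier would be 1.10-1.14%. The gap is negligible, which agrees with the protocol's remark.

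**Step 2: formulas.** With cumulative cause-specific hazards H1 (event) and H2 (other-cause death):
- one minus Kaplan-Meier = 1 - exp(-H1(t))
- cumulative incidence = integral from 0 to t of exp(-H1(u) - H2(u)) dH1(u)

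Check by hand with constant hazards, 34 deaths and 21.6% other-cause death: H2 = 0.2438. Taking one minus Kaplan-Meier as 2.33% gives H1 = 0.0236. Cumulative incidence = (0.0236/0.2674) × (1 - exp(-0.2674)) = 0.0882 × 0.2346 = 2.07%, which is 34/1643.

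**Step 3: prostate-cancer mortality at 15 years.** Event hazard constant or rising (Weibull shape 1 or 2), other-cause shape 1.5. H1 is solved so that the cumulative incidence equals deaths/1643.

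| Deaths | Cumulative incidence | 1-KM, 15% other-cause | 1-KM, 25% other-cause | Excess, points |
|---|---|---|---|---|
| 34 | 2.07% | 2.21-2.27% | 2.31-2.43% | 0.14-0.36 |
| 48 | 2.92% | 3.11-3.20% | 3.26-3.43% | 0.19-0.51 |
| 60 | 3.65% | 3.89-4.00% | 4.08-4.29% | 0.24-0.64 |
| 72 | 4.38% | 4.67-4.80% | 4.89-5.14% | 0.29-0.76 |

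The relative excess is 7-17%. Stretching to 30% other-cause death, with a rising event hazard and a constant other-cause hazard, gives at most 1.15 points (26% relative) at 72 deaths.

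**Step 4: progression.** If the Kaplan-Meier estimate is 25%, the actual risk is 22.9-23.55% at 15% other-cause death and 21.4-22.5% at 25%. The excess is about 1.5-3.6 points (6-17% relative).

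**Step 5: radical treatment under active monitoring.** If the Kaplan-Meier estimate is 60%, the actual uptake is 57.0-58.3% at 15% other-cause death and 54.8-57.0% at 25%, with a constant or front-loaded uptake hazard (shape 1 or 0.5). The excess is about 2-5 points (3-9% relative). A more front-loaded hazard (shape 0.3) gives 1.1-1.9.

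**Step 6: what does not move.** With 90% uptake within nine months in a radical arm (assumed), actual uptake is 89.9-90.0% against 90.0%. Ratios between arms hold: a true risk ratio of 1.5 gives 1.50 by Kaplan-Meier, and 2.0 gives 2.00. Overall survival has no competing event, and event rates per 1000 person-years are not distorted in this way.

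**The case against.** The strongest reply is that little of inferential weight is at stake. The three-arm test, the pairwise gate and the Cox hazard ratios are untouched. For prostate-cancer mortality the excess is smaller than the sampling error: the 95% half-width for one arm of 545 is 1.96 × sqrt(0.0207 × 0.9793/545) = 1.2 points at 34 deaths, and 1.7 points at 72. The protocol saw no such bias at 10 years. All of this stands and limits the severity. It does not remove the point: this is bias in one direction, it is larger for progression and uptake, and the 10-year remark rests on 17 deaths over a shorter horizon.

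A reader might infer more than the documents support:

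- **That every reported percentage is overstated.** Step 6 shows otherwise, and for the tabulated mortality percentages the SAP names no estimator, so their overstatement cannot be asserted.
- **That the SAP uses the age argument to defend its Kaplan-Meier curves.** The sentence follows the Cox model and speaks only of the treatment effect. The gap is that nothing covers the absolute risks.
- **That the 20-year results must inherit the problem.** Appendix 2 says the 20-year analyses will follow similar approaches to the 15-year ones, but its commitment to cumulative incidence covers both time points, and Protocol 5.5 (February 2022) postdates the SAP (November 2020).
- **That the SAP states that other-cause deaths are censored.** It does not. For Kaplan-Meier prostate-cancer-specific survival, censoring follows from the method. For progression, section 5.1 could be read as counting any death, in which case Kaplan-Meier would be correct; the Figure 3 legend points the other way.

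**Conclusion.** The point holds for the Kaplan-Meier-based absolute risks of prostate-cancer death, of progression (if the Figure 3 legend governs) and of radical-treatment uptake under active monitoring. Followed as written, the SAP would overstate these and would not deliver an analysis the protocol commits to.

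The size is modest for prostate-cancer mortality (about 0.1-0.8 percentage points) and larger for the assumed 25% progression risk (1.5-3.6) and 60% uptake (2-5). These figures depend on 15-25% other-cause death by 15 years and on the assumed hazard shapes; the direction does not. Because the primary comparison stays valid as a cause-specific effect, this is something that should be fixed rather than a barrier to the primary analysis.

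**What to change.** - In SAP 5.1, Figures 2, 3A and 3C, and the Table 1 mortality percentages, report Aalen-Johansen cumulative incidence with death from other causes as the competing event, and name that estimator. The protocol promises cumulative incidence as an addition; making it the main display goes a step further but is consistent with its stated reason.
- Keep Kaplan-Meier for overall survival.
- State how other-cause deaths are handled in the progression endpoint, so that section 5.1 and the Figure 3 legend agree.
- In 5.2, label the Cox hazard ratio cause-specific, say that the age argument applies to the hazard ratio only, and name the competing event as other-cause death.
- Carry the same wording into the 20-year plan.

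The cost is a few lines of SAP text and a standard software routine. No new data are needed beyond date and cause of death, which the trial already collects.
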